### Participant selection

Participants will be randomly assigned to one of two intervention groups and will be primarily recruited through the Stroke Recovery Association of New South Wales (NSW), Australia support group (Stroke Club) network. This Association holds regular Stroke Club meetings throughout NSW. The exercise classes will be conducted weekly in the venues used by the Stroke Club, prior to and after meeting times. It is anticipated that each Stroke Club will have participants randomised into both intervention groups and both types of classes will be offered at different times at the same venue. Additional participants will be recruited through advertisement and local physiotherapists and will attend the same exercise classes. To be eligible for the study, participants must be community-dwelling stroke survivors aged 40 years and above and be able to walk 10 m independently with or without a mobility aid.

Participants will be excluded if they have a Mini-Mental State Examination score [20] of < 20, have insufficient communication skills to participate in assessment and intervention, have a medical condition which precludes exercise (eg. unstable cardiovascular disease) or suffer from other uncontrolled chronic conditions that would interfere with the safety and conduct of the training and testing protocol.

All potential volunteers will be screened for eligibility by a physiotherapist. Medical clearance will be required from each participant's medical practitioner to certify him/her able to participate in moderate-intensity semi-supervised exercise before being accepted into the trial.

The study protocol has been approved by Sydney South West Area Health Service Ethics Committee (Clearance No: X06-0039) and The University of Sydney Human Research Ethics Committee (HREC Number 07/2006/9031), and written informed consent will be obtained from all participants.

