### Randomisation

After approval from the participant's usual General Practitioner and completion of the initial assessment, participants will be formally entered into the study and randomised to either the lower limb intervention or upper limb/cognition intervention group. Randomisation will be stratified by stroke club site using a computer generated random number schedule with variable block sizes 2–6. Generation of the randomisation sequence will be performed centrally by a researcher not involved in recruitment or assessment. Group allocation will be concealed using consecutively-numbered opaque envelopes. The opaque envelope will be opened after completion of the assessment in the presence of the participant.

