### Statistical analysis

The number of falls per person-year will be analysed using negative binomial regression to estimate the difference in fall rates between the two groups, adjusted for previous multiple faller status [30]. The proportion of fallers between groups will be compared using the relative risk statistic. Between-group comparisons of final test performance for the continuously-scored outcome measures will be made using General Linear Models (ANCOVA) controlled for pre-test performance. Ordinally-scored data will be analysed for between group differences using the non-parametric Mann Whitney U statistic. An intention-to-treat approach will be used for all analyses.

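### Stroke club site stratifies the randomisation but is absent from the covariates named for the fall-rate and ANCOVA models, so those tests are conservative to the extent that site is prognostic

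*Protocol article*

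**What the plan says.** In the protocol article, under Randomisation: "Randomisation will be stratified by stroke club site using a computer generated random number schedule with variable block sizes 2–6". Under Participant selection: "It is anticipated that each Stroke Club will have participants randomised into both intervention groups". Treatment is therefore compared mainly within sites.

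The Statistical analysis section states the adjustment for each comparison:

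- Fall rate (primary): negative binomial regression to "estimate the difference in fall rates between the two groups, adjusted for previous multiple faller status".
- Continuous outcomes, including walking speed and walking capacity (also primary): "Between-group comparisons of final test performance for the continuously-scored outcome measures will be made using General Linear Models (ANCOVA) controlled for pre-test performance".
- Fallers: "The proportion of fallers between groups will be compared using the relative risk statistic", with no covariate named.
- Ordinal outcomes: a Mann-Whitney test, with no stratification named.

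Site appears in none of these, whether as covariate, stratum or random effect. The Sample size section does not mention it either, and the article gives no reason for leaving it out.

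**The concern.** Small-block randomisation within site makes the two arms alike in site mix. A site effect common to both arms then largely cancels from the treatment difference, so the estimate is more precise than under unrestricted randomisation. A model without site does not see this. It keeps between-site variation in its residual (or, for the negative binomial, in its dispersion) and reports a standard error that is too large for the design. The test then rejects less often than its nominal level, and some of the precision bought by stratifying is not used.

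Site could well be prognostic. Members of one club share a locality and a class venue for twelve months, and site is the only stratifier that was chosen. Both primary outcomes are affected, and the sample size claims 80% power with no stated margin.

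**Working it through.** **1. The plan's own figure.** The Sample size section gives 350 participants (175 per group), 80% power, 5% level, incidence rate ratio (IRR) 0.66 and 15% loss. With a two-sided test assumed, evaluable n per arm = 175 × 0.85 = 148.75. The Wald formula is n = (1.960 + 0.842)² × [1/μ₀ + 1/(0.66μ₀) + 2k] / (ln 0.66)². Solving for the bracket gives 148.75 × 0.1727 / 7.849 = 3.27. The control rate μ₀ and dispersion k are not stated, so 350 is attainable but cannot be confirmed: μ₀ = 1.0 with k = 0.38 fits, and so does μ₀ = 2.0 with k = 1.01. The point does not depend on this figure.

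**2. Analytic size.** Let ρ be the share of residual variance lying between sites after baseline adjustment (assumed; not in the article). With allocation balanced within site:

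- reported SE / true SE = 1/√(1−ρ)
- type I error without site = 2[1 − Φ(1.960/√(1−ρ))]
- power without site, where its reported SE implies 80%, = Φ(0.842/√(1−ρ))
- power with site = Φ(2.802/√(1−ρ) − 1.960)

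| ρ | SE ratio | Type I, no site | Power, no site | Power, site | Gain (points) |
|---|---|---|---|---|---|
| 0.01 | 1.005 | 4.9% | 80.1% | 80.4% | 0.3 |
| 0.05 | 1.026 | 4.4% | 80.6% | 82.0% | 1.4 |
| 0.10 | 1.054 | 3.9% | 81.3% | 84.0% | 2.7 |
| 0.20 | 1.118 | 2.8% | 82.7% | 87.9% | 5.2 |

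**3. Linear-model simulation** (the ANCOVA case). N = 350, 15% loss, blocks of 2, 4 and 6 within 15 or 40 sites (assumed), effect 0.325 SD, site as fixed effects, 3,000 runs per cell. The Monte Carlo standard error is about 0.4 points for null rejection and 0.7 for power.

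| ρ | Sites | Null rejection, no site / site | Power, no site / site | Change (points) |
|---|---|---|---|---|
| 0 | 15 | 4.9 / 5.0% | 80.4 / 80.0% | −0.4 |
| 0 | 40 | 5.1 / 5.2% | 80.1 / 79.0% | −1.1 |
| 0.05 | 15 | 4.5 / 5.3% | 80.3 / 81.4% | +1.1 |
| 0.05 | 40 | 5.2 / 5.5% | 80.8 / 81.1% | +0.3 |
| 0.10 | 15 | 4.3 / 5.4% | 82.2 / 84.4% | +2.2 |
| 0.10 | 40 | 4.1 / 5.5% | 80.2 / 81.9% | +1.7 |
| 0.20 | 15 | 3.6 / 5.4% | 81.8 / 86.8% | +5.0 |
| 0.20 | 40 | 3.7 / 5.5% | 81.5 / 85.9% | +4.4 |

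The mechanism shows at ρ = 0.20 with 15 sites. Without site the mean reported SE is 0.115 against an actual sampling SD of 0.106 to 0.107; with site it is 0.104 against 0.105. The estimate itself hardly changes in variability. What changes is the reported SE.

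**4. Negative binomial simulation** (the fall-rate case). Assumed control rate 2 per year, dispersion about 1, 300 evaluable.

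- 15 sites, site log-rate SD 0.45, 1,000 runs: without site, mean SE 0.135 against an actual 0.129 and null rejection 3.4%; with site, null rejection 4.6%. Power at IRR 0.66 rose from 86% to 89%.
- Many small sites with fixed effects, up to 600 runs (Monte Carlo error about 1 point), null rejection without / with site: 25 sites of 12 and no site effect, 5.3 / 6.2%; 25 sites of 12 and log-scale site variance 0.1, 6.5 / 7.5%; 50 sites of 6 and no site effect, 5.0 / 7.3%. In the last case the mean SE with site was 0.134 against a true SD of 0.148, and 2% of fits failed. Many site parameters make the estimated dispersion, and hence the SE, too small.

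A random intercept was not simulated. It is preferred because it avoids estimating one parameter per site.

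**The case against.** The strongest reply is that a journal article condenses its analysis section and does not call its covariate list exclusive, so an unseen analysis plan may already include site. This has some weight, and the treatment of small sites is a detail that such a plan would normally carry. But the article goes beyond silence. It names a covariate for each regression model, and a plan that followed that wording would omit the one factor that the design balanced.

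The second reply is that the error is on the safe side and possibly trivial. That stands in part. A reader might infer a biased treatment effect or a false-positive rate above 5%. Neither follows: individuals are randomised within sites, and leaving out a balanced site effect makes the test conservative. A reader might also infer that intervals are certainly too wide and power certainly lost. The documents do not support that, since they give no number of sites and no ICC. At ρ = 0.01 to 0.05 the analytic SE excess is 0.5 to 2.6%, and some simulated cells at 0.05 show no conservatism at all.

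The third reply is that adjustment has its own cost. This stands. With no site effect and 40 sites, fixed effects lost about 1 power point, and in the negative binomial model fixed effects for many small sites raised type I error to about 6 to 8%. Part of any apparent power gain in such a model would come from that. It limits the form of the remedy; it does not defend leaving site out.

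**Conclusion.** The point holds as a mismatch between the stated randomisation and the stated primary models. Its direction is clear: if site is prognostic after baseline adjustment, the reported standard errors are too large and the tests conservative. Its size cannot be settled from the documents. Taking the calculations together, the gain from including site is about 0 to 2 power points at a residual ICC of 0.05 or below, and about 2 to 5 in linear-model simulation at 0.10 to 0.20.

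These figures rest on an assumed number of sites, assumed ICCs, a site effect common to both arms and, for falls, an assumed rate and dispersion. The fall-rate evidence agrees in direction where sites are few and large, but it is thinner than the linear-model evidence. This is a correction worth making because it is cheap and touches both primary outcomes. It does not threaten the validity of the trial.

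**What to change.** Add stroke club site to the two primary models, keeping the covariates already named:

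- Fall rate: negative binomial regression with multiple-faller history and, preferably, a random intercept for site. Avoid fixed effects for many small sites.
- Continuous outcomes: ANCOVA with the pre-test score and site, either as a random intercept or as a fixed effect with very small sites pooled by a rule set before unblinding.

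Optionally, stratify the supporting comparisons by site: a Mantel-Haenszel relative risk for fallers and a van Elteren test for ordinal outcomes. Both keep the kind of comparison already planned.

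The cost is a sentence or two of analysis wording and the small-site rule. No new data are needed, since site is known at randomisation. The statistical price is a slight loss of precision if site turns out not to be prognostic.

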### Sample size

As fall rates will be compared between groups using incident rate ratios (IRR) from negative bionomial regression models [30] we conducted an analysis of statistical power using the nbpower command in the STATA software package. A total of 350 participants (175 per group) will be recruited. The study will have 80% power to detect as significant at the 5% level a 34% reduction in the rate of falling (i.e. an IRR of 0.66 using negative binomial regression analysis) in the 12 month follow-up period. This allows for a 15% loss to follow-up due to death or withdrawal from the study. Experience from our previous work indicates that, with this sample size, power will also be sufficient to detect meaningful between-group differences for all other outcome measures [9,15,16].

## Discussion

It is widely accepted that in order to maintain health, physical activity is essential. Currently in the study area, routine provision of long term ongoing physical activity/exercise programs for people living in the community after stroke is virtually non-existent. There are a range of community-based physical activity programs for healthy older people. However, the chronic disability often associated with stroke means that these programs are not usually accessible for this population.

There is an urgent need to identify cost-effective evidence-based interventions for reducing falls and related injuries in people who has had a stroke. The WEBB program has been designed for falls prevention and so includes high challenge, yet safe, progressive balance exercises targeting standing balance and walking as well as progressive moderate to high intensity leg strengthening exercises with resistance applied using weighted vests. The program is currently also being evaluated in older persons recently discharged from hospital [31] and people with Parkinson's disease [32].

This project aims to investigate the effects of the WEBB program in community dwelling stroke survivors using a randomised controlled trial incorporating the features known to reduce bias (i.e. concealed random allocation to groups, blinded outcome assessment and intention to treat analysis) and large enough to detect any effect of the intervention on fall rates. This project will determine the effectiveness of the exercise intervention in reducing falls and enhance physical activity. In addition, we will also provide new knowledge about the potential for collaborating with existing community support groups in the provision of physical activity programs. Due to the partnership with NSW Stroke Recovery Association and their extensive network of stroke clubs, there is good potential for the proposed program to be incorporated into usual Stroke Club activities at the completion of the study period, if it is found to be effective. If this community-based exercise intervention is effective, this approach of utilising support groups could also have wide applications for other chronic diseases which are worsened by inactivity.
